#### Concealment mechanism

The Gorilla platform will complete the randomization by using a web-based randomization algorithm.

#### Sequence generation

Gorilla will randomly allocate participants to each of the study arms. Gorilla allows for two randomization options: (1) independent randomization of each individual based on a probability drawn, and (2) balanced randomization, which randomizes without replacement so that a fixed number of study participants end up in each study arm. To ensure that our experimental arms are balanced, we will employ the “balanced randomization” option.

### Intervention

The intervention consists of a collage of three SAS videos educating viewers about the importance of getting the COVID-19 vaccine to stop the spread of the virus. Created by our co-author MA for Stanford Medicine, all videos are animated with sound effects but do not include any words, speech, or text. The total duration of the collage is 4 min. The first video tells the story of a grandmother and her three family members, who are absorbed in their digital devices and completely ignore their grandmother. When a healthcare professional knocks on the door and offers them the COVID-19 vaccine, the daughter declines while the grandmother welcomes the healthcare professional and gets vaccinated. Visibly pleased, the grandmother explains to the family that polio and other infectious and deadly diseases would still exist without vaccination. Finally encouraged, the other family members agree to get the COVID-19 vaccine. In the second video, the fight against the coronavirus is represented in a video game scenario. The coronavirus is an evil particle that gains points by infecting people and levels up (develops into a variant) by jumping from person to person. The virus' triumph is over as soon as the people decide to deploy the COVID-19 vaccine as a defense which turns out to prevent new variants from emerging. The main character of the third video is an unhappy and sad man who walks down the street and is denied access to shops, clubs, and means of transportation. Suddenly he meets a doctor who offers him a shot against COVID-19. After getting vaccinated, all those activities forbidden to him up to that moment are now available and his mood changes from forlorn to happy. To maximize cross-cultural appeal, the figures were purposefully depicted without distinguishable cultural identification, while the background music is entertaining and geared to increase interaction and user sharing of the videos on social media (28). The videos are interspersed with black screens reporting short facts about the COVID-19 vaccine.

We will compare the SAS intervention videos about COVID-19 vaccine with an APC video (arm 2), and no video (arm 3). Developed by our co-author (MA) for Stanford Medicine in collaboration with the IASC, UNICEF, and the WHO, the APC video is similar in style to the SAS intervention videos; it is also animated, with a duration of 4 min, and aims to convey messages of hope, solidarity and empowerment to kids and their caregivers (no health or COVID-19 vaccine-related messages). The APC video will mimic the inactive component of the intervention, i.e., the video format, but not the active component of the intervention, i.e., the message about COVID-19 vaccine. This will allow the content effect of the COVID-19 vaccine intervention videos to be isolated.

Lastly, the comparison between the intervention SAS videos against COVID-19 and the no-video task will allow us to measure the total effect of the intervention.

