## Methods and analysis

### Trial design

We will conduct a randomized controlled trial (RCT) following a multi-site, parallel group design with post-trial access to treatment (see Figure 1). After completing demographic, vaccine, and political beliefs surveys, participants will be randomly assigned to one of three arms: an intervention arm exposing participants to the SAS video collage (arm 1), an attention placebo control (APC) arm showing a video of similar length unrelated to the vaccine (arm 2), or a control arm without any intervention (arm 3). We will randomize the participants in a 1:1:1 ratio to the trial arms. In the intervention arm, participants will watch a collage of three SAS videos underlining the importance of COVID-19 vaccination to provide study participants with access to evidence-based information regarding their risk of contracting and spreading the COVID-19 virus (arm 1: COVID-19 vaccine message) (23). In the APC arm, participants will watch a video that shows how important it is to help children find hope in the future (arm 2: no COVID-19 vaccine message) (24). In the control arm, participants will receive no intervention (arm 3: no video). Participants in arm 1 and arm 2 will not be able to pause or skip the video.

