##### Attention questions

We will conduct attention questions to establish whether interventions were actively viewed and not merely skipped or played in the background while the person engaged in other tasks (one information attention question per video). Respectively, the question pool comprises the following questions:

The video describes the difference between Pfizer and Moderna vaccines (arm 1) – [False].The video is about a fantasy creature who travels the world helping children find hope in the future and joy in simple pleasures (arm 2) – [True].

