#### Secondary outcome measures

Components of the complexity of vaccine hesitancy that have been identified in the research, namely COVID-19 risk and benefit perception, social norms, hope, and optimism, are secondary outcomes that we hypothesize will change as a result of the intervention. Therefore, all participants will be asked to complete questionnaires measuring their perceptions of severity and susceptibility, response efficacy, attitude, self-efficacy, social norms, as well as questions relating to optimism, hope, and trust.

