### Strengths and limitations

This study will use an RCT design to assign individuals to watch a collage of three SAS videos about COVID-19 vaccine (arm 1), an APC video (arm 2), or no video (arm 3). The videos in arm 1 and arm 2 are identical in length (~4 min each) and similar in style. The randomization to the three trial arms will reduce the likelihood that systematic differences in groups may influence outcomes and will let us isolate the true effect of the SAS intervention videos.

The inclusion of the APC video is a novel component of our study that will allow us to quantify the content effect of the intervention. We define the difference between the SAS intervention videos and the control as the total effect, the difference between the SAS intervention videos and the APC video as the content effect, and the difference between the APC video and the control as the attention effect. There have been several entertainment-education studies that have employed an experimental approach to assess the effect of an intervention video in this way (47–51), but only few on COVID-19 (44, 45, 52).

In each of the three arms, we will run a list experiment to measure behavioral intent while eliminating social desirability bias. It is likely that participants will already be primed to give socially acceptable responses to questions about their views on the COVID-19 vaccine. The indirect questions (i.e., how many statements do you agree with) provide protection to participants if they want to reject the vaccine message without revealing this intention. To the best of our knowledge, few studies have employed a list experiment approach to assess the efficacy of an entertainment-education video in improving a specified health outcome (51, 52). Hence, we are aware that during the study our strategy could prove to have unforeseen disadvantages. Moreover, list experiments are focused on short-term effects of the intervention, which leaves us with uncertainty regarding the question if a SAS video would actually lead participants to get vaccinated in the near future.

Another objective is assessing participants' voluntary engagement with the SAS videos among participants assigned to the APC and control arms (post-trial access to treatment). The findings of this study will assist us in evaluating participants' willingness to watch online SAS videos, particularly when this willingness is weighed against a time cost, simulating a real-world scenario.

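### The attention-placebo video is about hope, so for the hope and optimism outcomes its contrasts may not be readable as content and attention effects

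*Protocol article*

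**What the plan says.** The protocol article presents the APC video as hope-themed in three places. Under Trial design, arm 2 sees "a video that shows how important it is to help children find hope in the future". Under Intervention, the video "aims to convey messages of hope, solidarity and empowerment to kids and their caregivers". Under Attention questions, the arm 2 item, keyed true, reads "The video is about a fantasy creature who travels the world helping children find hope in the future and joy in simple pleasures".

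The Intervention section also gives the video its methodological role: "The APC video will mimic the inactive component of the intervention, i.e., the video format". The active component is said to be the COVID-19 vaccine message, which the APC video lacks, and the contrast is meant to isolate the effect of content.

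Outcomes and Secondary outcome measures both name hope and optimism; the latter says that "hope, and optimism, are secondary outcomes that we hypothesize will change as a result of the intervention". Both are measured after the video, hope with the Adult Hope Scale and optimism with a five-item scale.

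Strengths and limitations defines "the difference between the SAS intervention videos and the APC video as the content effect", APC minus no video as the attention effect, and SAS minus no video as the total effect. None of these definitions is restricted to particular outcomes. The secondary objective at the end of the Introduction is to explore differences in the individual factors between the three arms after the interventions, and the paragraph before the objectives lists hope and optimism among those factors.

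**The concern.** An attention placebo supports a split into content and attention only if it is inert for the outcome being analysed. This video's subject is hope in the future, and hope and optimism are two of the measured outcomes. One of the five optimism items asks directly about hope for one's own future.

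If the APC video raises hope or optimism at all, a vaccine video with no effect on them could look harmful beside it, and a real benefit could be masked. What is reported as an attention effect could be the effect of a hope message. The limitations text does not mention the overlap; it presents the APC video as a strength of the design.

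**Working it through.** The plan gives no figure to reproduce on this point. The check is the algebra of the three contrasts, followed by an illustration of scale.

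**Inputs**
- Total sample 10,000 (Sample size calculation), allocated 1:1:1 (Trial design): 10,000 / 3 ≈ 3,333 per arm, before any attrition.
- Two-sided 5% level and 80% power, giving 1.960 + 0.842 = 2.802.
- d = effect of the SAS videos, and e = effect of the APC video, each against no video and in SD units. The document gives neither, so all values below are assumptions.

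**Contrasts for hope or optimism**
- Arm 1 minus arm 3 (total effect) = d
- Arm 1 minus arm 2 (labelled content effect) = d − e
- Arm 2 minus arm 3 (labelled attention effect) = e

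The second contrast is the effect of SAS content net of format only if e is purely a format and attention effect. Any part of e that comes from the hope message is subtracted one-for-one from the content effect and counted in full as attention. The total effect does not involve e.

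**Smallest difference detectable with 80% power**

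SE = sqrt(2 / 3,333) = 0.0245 SD; 2.802 × 0.0245 = 0.0686 SD.

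So with d = 0 and e ≈ 0.07 SD, arm 1 minus arm 2 is about −0.07 SD and would be significantly negative about 80% of the time.

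**Range, assuming d = 0.10 SD**

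Power ≈ Φ(|d − e| / 0.0245 − 1.960). For example, 0.05 / 0.0245 = 2.04, and Φ(0.08) ≈ 53%.

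| e (assumed) | Arm 1 − arm 2 | Chance of a significant result | Arm 1 − arm 3 | Power |
|---|---|---|---|---|
| 0 | 0.10 | 98% | 0.10 | 98% |
| 0.05 | 0.05 | 53% | 0.10 | 98% |
| 0.10 | 0 | 5% | 0.10 | 98% |
| 0.15 | −0.05 | 53%, against SAS | 0.10 | 98% |
| 0.20 | −0.10 | 98%, against SAS | 0.10 | 98% |

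Because the sample is large, even a small comparator effect could hide or reverse an SAS effect of similar size. Arm 1 versus arm 3 is untouched.

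**The case against.** Several counter-arguments have force.

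- **The effect is not demonstrated.** The document says what the video aims to convey, and to children and their caregivers. Several Adult Hope Scale items concern past success and general problem-solving, which a 4-minute animation may not shift. This stands: e may be near zero. A reader might infer that the placebo is known to be active and the content effect known to be biased; the document supports neither statement. It does show that inactivity is asserted for outcomes that match the video's own theme.
- **Randomization protects the comparison.** This stands. Arm 1 minus arm 2 is an unbiased estimate of the difference between the two videos. Only its reading as content net of format is in question.
- **No such contrast is written out for these outcomes.** Statistical methods for primary and secondary outcomes spells out the content effect only for the list experiment, and its list of scored factors omits hope and optimism. This is correct. The problem arises from the unrestricted definitions in Strengths and limitations together with the three-arm objective. No text exempts the two outcomes.
- **Inactivity is already framed against vaccine content, and arm 3 exists.** Partly so. The needed contrast is in the design, but the labels are not limited to vaccine outcomes.

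A reader might also infer that the arm 2 attention item primes the scales immediately before they are answered. The order under Trial design does not support that: the knowledge questions (scored 0 to 24) and 14 Likert items come in between.

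**Conclusion.** The point holds for hope and optimism only. For these two secondary outcomes the protocol's own description of the APC video does not support treating it as format alone, so SAS minus APC and APC minus no video may not be interpretable as content and attention effects.

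The size cannot be derived from the document. The figure of about 80% assumes an APC effect of about 0.07 SD, no SAS effect, and 3,333 analysed per arm. The 10,000 is also meant to cover attrition, so fewer may be analysed and the detectable difference would then be somewhat larger than 0.0686 SD.

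It would be tempting to extend the point to the content effect as a whole. The document does not support that: the APC video carries no health or vaccine message, so vaccine knowledge and behavioral intent are not implicated. This is a matter of interpretation for two named secondary outcomes and is worth correcting before results are read.

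**What to change.** For hope and optimism:

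- Name arm 1 versus arm 3 (total effect) as the interpretable test.
- Report arm 2 versus arm 3 as the effect of a hope-themed video, not as an attention effect.
- State that arm 1 versus arm 2 is a comparison with a hope-themed video and is not interpreted as a content effect.

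In the Intervention section, limit the claim of inactivity to vaccine-related outcomes. In Strengths and limitations, limit the content and attention definitions in the same way and add the overlap as a limitation. Keep the content contrast for knowledge, intent and vaccine perceptions.

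The cost is wording in the protocol and in any analysis plan; no new arm or data are needed. The price is that, for hope and optimism, the effect of content cannot be separated from that of attention.

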### Outcomes

The primary outcome of this study is the effectiveness of the SAS intervention video in increasing knowledge about the COVID-19 vaccine. While knowledge alone is insufficient to modify health behaviors, it is vital for individuals to access and comprehend their health options in order to exert greater control over their health decisions (29, 30). Furthermore, as a second primary outcome, we will measure changes in behavioral intent toward the COVID-19 vaccination. According to the Theory of Planned Behavior (TPB), the intention to act is considered the immediate determinant of action. In this study, behavioral intent is defined as a participant's commitment to receive the COVID-19 vaccine and to seek information about the vaccine during the next two weeks (31). As a third primary outcome, we will evaluate participant willingness (quantification) to voluntarily engage with the SAS intervention videos (post-trial access to treatment) to determine whether SAS videos may have the potential to generate interest as a precursor for health promotion and communication.

As secondary outcomes, we will focus on COVID-19 risk and benefit perception, social norms, hope, and optimism that we hypothesize will change as a result of the intervention.

#### Primary outcome measures

The specific primary outcomes are to improve COVID-19 vaccine knowledge, to increase behavioral intent toward COVID-19 vaccine, and to quantify intrinsic interest in watching a SAS video about COVID-19 vaccine.

##### Attention questions

We will conduct attention questions to establish whether interventions were actively viewed and not merely skipped or played in the background while the person engaged in other tasks (one information attention question per video). Respectively, the question pool comprises the following questions:

The video describes the difference between Pfizer and Moderna vaccines (arm 1) – [False].The video is about a fantasy creature who travels the world helping children find hope in the future and joy in simple pleasures (arm 2) – [True].

##### Knowledge

To determine if the SAS intervention video increases participants' knowledge of the COVID-19 vaccine, all participants will be asked true/false questions that are spread over a total of three parts:

**Part 1**

Which of the following are diseases that have nearly been eradicated by vaccines? Choose True or False for each:

Polio has nearly been eradicated by vaccines.Smallpox has nearly been eradicated by vaccines.Malaria has nearly been eradicated by vaccines.Rubella has nearly been eradicated by vaccines.Tuberculosis has nearly been eradicated by vaccines.Lyme Disease has nearly been eradicated by vaccines.Measles has nearly been eradicated by vaccines.HIV has nearly been eradicated by vaccines.Mumps has nearly been eradicated by vaccines.Tetanus has nearly been eradicated by vaccines.West Nile Fever has nearly been eradicated by vaccines.Diptheria has nearly been eradicated by vaccines.

**Part 2**

It is not recommended for pregnant and breastfeeding women to get vaccinated against COVID-19.It is not recommended for immunocompromised people to get vaccinated against COVID-19.

**Part 3**

Which of the following are common side effects of vaccination with the COVID-19 vaccine?

Sore arm is a common side effects of vaccination with the COVID-19 vaccine.Chest pain is a common side effects of vaccination with the COVID-19 vaccine.Fever is a common side effects of vaccination with the COVID-19 vaccine.Chills are a common side effects of vaccination with the COVID-19 vaccine.Nausea is a common side effects of vaccination with the COVID-19 vaccine.Shortness of breath is a common side effects of vaccination with the COVID-19.Racing heart is a common side effects of vaccination with the COVID-19 vaccine.Body aches are a common side effects of vaccination with the COVID-19 vaccine.Headache is a common side effects of vaccination with the COVID-19 vaccine.Body rash is a common side effects of vaccination with the COVID-19 vaccine.

##### COVID-19 perception

In addition, we ask about the participants' current attitude regarding COVID-19 and their self-perceived risk assessment:

I believe COVID-19 is severe.I believe COVID-19 is serious.I believe COVID-19 is significant.I am at risk for COVID-19.It is likely that I will get COVID-19.It is possible that I will get COVID-19.

##### Behavioral intent

A list experiment approach will be used to assess behavioral intent to be vaccinated as well as obtain and disseminate credible and evidence-based information on the COVID-19 vaccine (see Table 1 for list experiment and respective list items). The control group will be given a list of four items, while the treatment group will be given the same list plus one additional sensitive item. The sensitive item comprises the willingness to read information about the COVID-19 vaccine from official sources, speaking with a health professional about a COVID-19 vaccine, receiving the required dose of a COVID-19 vaccine, learning about the risks and benefits of receiving a COVID-19 vaccine, and sharing information about the COVID-19 vaccine. Participants will be asked how many of the items on the list they agreed with, without indicating which ones. The minimum score for each list is zero, and the maximum score for the control list is four, and five for the treatment list. We designed the list items to minimize ceiling and floor effects (32). We will assess the proportion of participants who agreed with the sensitive item, that is, behavioral intent toward SAS created by health professionals, by comparing the average difference between the treatment and control lists. The items in each list will be randomly arranged to prevent exposing the participant to the purpose of the list experiment, as well as to eliminate order effects (random order).

**Table 1 T1:** List experiment items (treatment item is *underlined*).

**Lists**	** *List items* **
**List 1: Education**	*In the next 2 weeks, I will…* • Go grocery shopping for me/my family. • Read the latest news on social media channels. • Pick a fight with my partner about COVID-19 precautions. • Use an online grocery delivery service. • *Read information from official sources, like about COVID-19 vaccine*.
**List 2: Healthy behavior**	*In the next 2 weeks, I will..*. • Wash fruits and vegetables with soap. • Do the laundry. • Learn more about alternative medicine. • Wash my hands every day for at least 20 s. • *Talk to a health worker about COVID-19 vaccine*.
**List 3: Moral obligation**	*In the next 2 weeks, I will..*. • Go out with my friends on at least one evening. • Visit a local community health center. • Develop my own smartphone app for tracking the spread of COVID-19. • Take out the garbage at least once per month. • *Get the needed dose of COVID-19 vaccine*.
**List 4: Perceived action efficacy (benefits)**	*In the next 2 weeks, I will..*. • Write and publish my own article about COVID-19. • Spend time chatting with my friends online. • Practice meditation daily. • Do the vacuuming in my house/apartment. • *Learn about risks and benefits of getting a COVID-19 vaccine*.
**List 5: Advocacy**	*In the next 2 weeks, I will..*. • Clean kitchen counters and dishes after use. • Have alcoholic drinks on at least three evenings. • Spend time on the internet. • Measure my body temperature at home daily. • *Share information about COVID-19 vaccine from official sources with my friends and family*.

Each list experiment will be preceded by the question “How many of the five/six statements do you agree with? We don't want to know which ones, just answer how many. In the next 2 weeks, I will...”

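### The List 1 sensitive item in Table 1 does not match its definition and, if fielded as printed, can be read as broader than COVID-19 vaccine information

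*Protocol article*

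**What the plan says.** The second primary outcome is behavioral intent. The Outcomes section defines it as a commitment to be vaccinated and "to seek information about the vaccine during the next two weeks". It is measured with five list experiments. In each, a participant sees either four neutral items or the same four plus one sensitive item, and reports only how many he or she agrees with.

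The Behavioral intent section lists the content of the five sensitive items in prose. The first is "the willingness to read information about the COVID-19 vaccine from official sources". Table 1, directly below, prints the List 1 item as "Read information from official sources, like about COVID-19 vaccine".

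The section on statistical methods for primary and secondary outcomes averages the treatment and control lists for each list experiment in each arm. The video effect is then the arm-by-list interaction in an OLS model (Equation 2). The article gives the List 1 item wording nowhere else.

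**The concern.** A list experiment estimates the share of people who agree with the added item exactly as it was shown to them. No follow-up question reveals why someone counted it. If the item lets people agree because they will read official information on some other subject, their agreement enters the List 1 estimate and cannot be removed later.

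Two things are then at stake. The List 1 estimate could not be read cleanly as intent to seek vaccine information, which is the stated outcome. And a video effect on that intent could look smaller than it is, because people who would agree anyway have no room to move. A broader item is also less sensitive, which weakens the stated reason for using a list experiment at all. The other lists do not repair this, because each list is averaged and contrasted separately.

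**Working it through.** **Wording, side by side.** No figure in the plan tests this point, so the main check is textual.

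| Place | Wording | Object of the behavior |
|---|---|---|
| Outcomes section | "to seek information about the vaccine during the next two weeks" | the vaccine |
| Behavioral intent, prose | "the willingness to read information about the COVID-19 vaccine from official sources" | the vaccine |
| Table 1, List 1 | "Read information from official sources, like about COVID-19 vaccine" | unclear: official sources in general, or the vaccine |
| Table 1, List 2 | "Talk to a health worker about COVID-19 vaccine" | the vaccine |
| Table 1, List 4 | "Learn about risks and benefits of getting a COVID-19 vaccine" | the vaccine |
| Table 1, List 5 | "Share information about COVID-19 vaccine from official sources with my friends and family" | the vaccine, with official sources as qualifier |

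The List 3 item is about getting the needed vaccine dose and is equally direct. List 5 shows that the authors use a clear word order elsewhere for the same two elements. Only List 1 has the construction with *like*.

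**What a broad reading could do (illustration, not an estimate).**

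Inputs from the Protocol article:
- list SDs of 0.85 and 1.0 (Sample size calculation);
- 10,000 participants, three arms 1:1:1, and lists 1:1 within arm, hence 10,000/6 ≈ 1,667 per cell.

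Inputs that are assumptions:
- D, a video effect between arms on true vaccine-information intent, set at 0.15 (15 points) or 0.10;
- g, the share who would agree with the broad item whatever their intent about the vaccine;
- g independent of who can be moved by the video, so that the visible effect is D(1 − g);
- two-sided alpha of 0.05.

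SE of the arm-by-list contrast = √[2(0.85² + 1.0²)/1,667] = √(3.445/1,667) ≈ 0.0455.

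Power ≈ Φ(D(1 − g)/0.0455 − 1.96).

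| g | Visible effect, D = 0.15 | Power |
|---|---|---|
| 0 | 0.150 | 91% |
| 0.10 | 0.135 | 84% |
| 0.25 | 0.113 | 70% |
| 0.50 | 0.075 | 38% |
| 0.75 | 0.038 | 13% |

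For D = 0.10, power falls from 60% at g = 0 to 20% at g = 0.50. The result runs from no loss to a severe one, and it turns on g, which the article does not give.

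**The case against.** The strongest reply is that this may be no more than a printing slip. The phrase is ungrammatical, and a source name may have dropped out after *like*. The item would then agree with its definition. The same section is loose elsewhere: the stem under Table 1 speaks of five or six statements, while the lists have four or five. The table therefore cannot be taken as verbatim screen text. This stands, and it is why the point is conditional. It does not remove the need to act, because either explanation leaves the instrument table of a primary outcome in need of the same correction.

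Several stronger readings are tempting, and the document does not support them.

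- *List 1 does not measure vaccine-information intent.* The item still names the COVID-19 vaccine. By the Trial design section, participants reach the lists after vaccine knowledge, risk, benefit and attitude questions, which favors the vaccine reading. At worst the measure is contaminated to an unknown degree.
- *The effect is diluted, by the amounts in the table above.* The shares g have no source in the article. The 0.15 in the Sample size calculation is the difference between control and treatment lists, that is, about 15% agreement with a sensitive item. It is not a video effect between arms. If that 15% were taken as g with D = 0.15, the visible effect would be 0.1275 and power Φ(0.1275/0.0455 − 1.96) ≈ 80%. If the people who can be moved are mainly those who do not otherwise use official sources, dilution is smaller still.
- *The behavioral-intent outcome as a whole is compromised.* The vaccination item (List 3) and the three other vaccine-information items (Lists 2, 4 and 5) are untouched.
- *Table 1 has a second fault of the same kind.* The List 3 control item "Take out the garbage at least once per month" does sit badly under a two-week stem. But it can be answered, and it appears identically on both lists, so it cancels in expectation from the list difference. No bias is shown. It is a tidy-up and not part of this point.

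**Conclusion.** The point holds as an internal inconsistency in the wording of one primary-outcome item. The consequence depends on which text is fielded. With the intended wording there is no loss. With the printed wording, List 1 is open to a reading broader than the stated outcome, and a video effect on vaccine-information intent could be attenuated by an amount that cannot be sized from the article. The power figures show only how such attenuation would act under stated assumptions. The matter is modest in scope, but worth settling before launch because no later analysis can recover the intended construct from the counts.

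**What to change.** Before launch, print and field the List 1 sensitive item in the words of its own definition, "the willingness to read information about the COVID-19 vaccine from official sources", starting at the verb *read*, so that the vaccine is unambiguously what is read about. Check the List 1 screen in the planned 1,000-person pilot; Table 2 already schedules a revision of the full study after it. The cost is one line of text on the survey platform.

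If the printed wording has already been shown to participants, state the exact fielded text and interpret List 1 as broader than vaccine-information intent. That costs only a sentence in the report, but the narrower interpretation of List 1 is then lost.
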